## Abstract

**Background:**

The capacity to form romantic relationships and sexual health of adolescents in the Netherlands are compromised by several factors, including young age of first intercourse and adolescent depression. Several thresholds like own expenses, trust and embarrassment prevent adolescents to seek help for their sexual problems. To overcome these thresholds, brief sex counselling has been developed. It has been used since 2006 within the Rotterdam-Rijnmond Public Health Service, but there is lack of information about the (cost-) effectiveness. In the current study we will evaluate the (cost-) effectiveness of brief sex counselling for sexual problems in adolescents and young adults between 18 and 25 years of age.

**Methods:**

In a randomised controlled trial we will compare (1) brief sex counselling with (2) intensive sexological treatment, and (3) delayed treatment (waiting list). Embedded in this RCT will be a trial-based economic evaluation, looking at the cost-effectiveness and cost-utility of brief sex counselling versus the two other interventions. Four hundred fifty adolescents (aged 18-25) with sexual problems will be recruited among the persons who visit the Public Health Service (PHS) and through various websites. After a screening procedure, eligible participants will be randomly allocated to one of the three intervention groups. Primary outcome measure of the clinical evaluation is the severity of sexual problems. Other outcomes include psychological distress, especially depression. The economic evaluation will be performed from a societal perspective. Costs will be assessed continuously by a retrospective questionnaire covering the last 3 month. All outcome assessments (including those for the economic evaluation) will take place via the internet at baseline, and at 3, 6, 9, and 12 months after baseline.

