### Outcome measures

Several instruments will be used to assess the effects of brief sex counselling on sexual functioning, depression and other psychological and physical complaints, and on secondary outcomes. Furthermore instruments will be used to assess the cost-effectiveness of brief sex counselling from a social perspective. The outcomes will be measured before randomization (during initial screening), at baseline and at 3, 6, 9 and 12 months after baseline (Additional file 1).

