#### Sexual functioning

##### Questionnaire for the Screening of Sexual Dysfunctions

The Questionnaire for the Screening of Sexual Dysfunctions (QSSD) [29,30] is a self-report instrument with 70 items, each assessed using a 5-point or a 7-point Likert-scale, which aims to measure the presence (and level) of sexual difficulties. This instrument has different versions, dependent on gender, partnered status and gender of the partner. Anchor points used are 'almost never' and 'always' for frequency and 'no trouble' and 'very much trouble' for associated distress.

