##### Female Sexual Functional Index

The Female Sexual Functional Index (FSFI) [32] is a multidimensional self-report instrument with 19 items, with responses assessed using a 6-point Likert-scale, which aims to measure sexual functioning on the dimensions of sexual desire, arousal, lubrication, orgasm, satisfaction and pain. High score indicates healthy sexual functioning. Its sound psychometric properties have been proven [35].

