##### International Index of Erectile Function

The International Index of Erectile Function (IIEF) [31] is a multidimensional self-report instrument with 15 items, assessed using a 6-point Likert-scale, meant to measure male sexual functioning on the dimensions of erectile functioning, orgasmic functioning, sexual desire, intercourse satisfaction and overall satisfaction. A high score indicates healthy erectile functioning. Its sound psychometric properties have been proven [31].

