### Recruitment

Participants will be recruited through different routes; referrals from Rotterdam-Rijnmond PHS, southern South-Holland PHS, Hollands-middle PHS, Maastricht/Heerlen PHS, Sense, and various websites. Adolescents who visit the PHS for a STI or Sense consult, and who report sexual problems, will be asked if they are interested in participating in the study. Adolescents who visit websites providing sexual information, like http://www.sense.info, can click on a banner if they are interested to participate. After thus reporting their interest, they receive an email containing information about the study protocol, and an informed consent (IC) form. Adolescents who return their signed IC form receive login codes for the questionnaires on the internet. Participants who score above the cut-off score on the QSSD and IIEF/FSFI, and meet the inclusion criteria are included in the study. Participants who do not meet the inclusion criteria are offered suitable alternative treatment options.

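### The primary outcome is named only as a construct, so any of three sexual-function scales, covering different populations, could decide the trial

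*Protocol article*

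**What the plan says.** **Primary outcome.** The abstract (Methods) says "Primary outcome measure of the clinical evaluation is the severity of sexual problems" and continues: "Other outcomes include psychological distress, especially depression". That is the only place where a clinical outcome is called primary.

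**Candidate instruments.** The Outcome measures section places three scales under sexual functioning and marks none of them as primary.
- QSSD: a scale "which aims to measure the presence (and level) of sexual difficulties". It has versions for gender, partnered status and gender of the partner, so it covers everyone.
- FSFI: a scale "which aims to measure sexual functioning on the dimensions of sexual desire, arousal, lubrication, orgasm, satisfaction and pain". The Participants section assigns it to women.
- IIEF: a scale "meant to measure male sexual functioning on the dimensions of erectile functioning, orgasmic functioning, sexual desire, intercourse satisfaction and overall satisfaction". The Participants section assigns it to men.

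Eligibility does not single one out either: "Participants who score above the cut-off score on the QSSD and IIEF/FSFI, and meet the inclusion criteria are included in the study".

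**Labels.** The opening of Outcome measures speaks of effects on "sexual functioning, depression and other psychological and physical complaints, and on secondary outcomes". Only the CEQ, SEAR, TSQ and the demographic questionnaires stand under the Secondary outcomes heading. Outcomes are collected "at baseline and at 3, 6, 9 and 12 months after baseline", and no time point is marked as primary.

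**Sample size and analysis.** The Sample size section plans for d = 0.40 (0.41 in the calculation) with 95 per group at two-sided 0.05, and attaches the effect to no scale. Clinical analyses computes difference scores for all outcome variables and compares the three arms by MANOVA. It proceeds to independent-groups t-tests only if the MANOVA is significant. No adjustment of those t-tests is stated.

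**The concern.** A primary outcome protects the trial's main conclusion only if the reader can tell beforehand which number will decide it. Here the construct could be read as the QSSD in all participants, the FSFI in women or the IIEF in men. These are different measures, taken in different people, and can disagree. The plan does not say how the FSFI and IIEF would be combined.

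Because all of them are tested and none is designated, a benefit on any one could be reported afterwards as the primary result. What is at stake is the false-positive rate of the headline claim and the interpretability of the planning effect, which belongs to no stated measure.

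**Working it through.** **Inputs from the protocol article.** Two-sided alpha 0.05 and 95 per group (Sample size); three sexual scales, two of them sex-specific (Outcome measures, Participants); t-tests only after a significant MANOVA (Clinical analyses). The article gives no error rate for this step, so there is no stated figure to reproduce. The point does not depend on whether the 95 per group is right.

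**Assumptions, not in the article.** Half of each arm are women. All outcomes share one within-person correlation ρ of 0.3, 0.5 or 0.7. One time point and one contrast (brief versus delayed) are considered. Test statistics are treated as normal. The MANOVA is approximated by a 5% chi-square test on 4 degrees of freedom over four outcomes: QSSD, the sex-specific scale pooled over sexes, CES-D and BSI.

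**Step 1: tests after the gate, sexual scales all null.** FSFI in women and IIEF in men use different people and are independent:

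1 − 0.95² = 0.0975.

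The QSSD statistic pools both sexes, z = (z_women + z_men)/√2, so its correlation with each sex-specific statistic is ρ/√2 (0.354 at ρ = 0.5). Simulating P(any |z| > 1.96) over 1,000,000 draws gives the second column of the table.

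**Step 2: add the gate, nothing differs anywhere.** Count only draws in which the gate also opens (third column).

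**Step 3: add the gate, depression truly differs.** Shift the CES-D statistic by 2.8 standard errors and leave the sexual scales null (last two columns). With 95 per arm this is 2.8 × √(2/95) = 0.41 SD, about the plan's own planning effect.

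| ρ | No gate | Gate, nothing differs | Gate opens (CES-D effect) | False positive on a sexual scale and gate open |
|---|---|---|---|---|
| 0.3 | 0.141 | 0.028 | 0.69 | 0.118 |
| 0.5 | 0.136 | 0.026 | 0.82 | 0.125 |
| 0.7 | 0.131 | 0.024 | 0.97 | 0.129 |

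As the true effect on the other outcome grows, the last column rises to the no-gate column.

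**Step 4: cross-check with a real MANOVA.** A separate simulation used three arms of 95, a Pillai test and then unadjusted t-tests. With nothing differing, it gave about 3% for brief versus delayed. With one of four to five outcomes truly differing by 0.4 to 0.8 SD, the chance of a false positive among the remaining outcomes was about 11 to 18% for that contrast. The set of outcomes is not the same as in Step 3, but the pattern is: the gate protects the global null only.

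**Step 5: after the fix.** One named score, time point and contrast, tested outside the MANOVA, has error 0.05.

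**The case against.** **The gate.** The plan does not run the t-tests freely. If no outcome differs, the MANOVA keeps the error for brief versus delayed at about 2 to 3%. This stands. An error rate of about 14% quoted without the gate would be wrong as a general statement. What remains is that control is lost once some other outcome truly differs, and the trial itself predicts an effect on depression (Background).

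**Depression and distress as further primary outcomes.** A reader might infer from the outcome section that CES-D and BSI are also primary, because they stand outside the block headed as secondary. The text does not support this. That section never uses the word primary, and the abstract expressly puts distress and depression among the other outcomes. By the same logic the SF-36, the personality questionnaire and costs would be primary too. The headings are mainly domains. This part is loose labelling to be tidied, not a second primary set.

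**Loss of power.** A reader might also infer that a sex-specific scale would leave the trial with about half its power. That needs an even sex split, a single-time-point t-test and a decision resting on one sex alone, none of which the article states. The point does not rely on it.

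**Condensed source.** The full protocol, the SAP and Additional file 1 are not shown, and scoring details may be there. This is fair for scoring. It is weaker for the identity of the primary measure: the article describes every instrument, uses the word primary, and does not connect the two.

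**The QSSD is not self-defining.** It has 70 items on mixed 5- and 7-point scales, covering frequency and distress, in several versions. Naming the instrument alone would leave the endpoint open. This stands and shapes the fix.

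**Conclusion.** The concern holds in this form: the single primary construct is tied to no instrument, three scales in different populations could fill it, and the analysis tests all of them without stated adjustment once the MANOVA is significant.

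If nothing differs, error stays at or below about 5%. If another outcome truly differs by about 2.8 standard errors, the chance of a false positive on at least one sexual scale is about 12 to 13% for brief versus delayed treatment, against 5% for one named measure. These figures rest on an assumed even sex split, correlations of 0.3 to 0.7 and an approximate gate. They do not count the further choice among four follow-up times or three pairwise contrasts. The mismatch in labels between the abstract and the outcome section is a minor inconsistency alongside this.

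**What to change.** - Name one primary measure of severity before any outcome data are seen. The QSSD is the natural choice: it is described as measuring the level of sexual difficulties and is the only one of the three given to both sexes.
- State exactly which QSSD score is used and how it is made comparable across the versions.
- State one primary time point, and brief counselling versus delayed treatment as the primary contrast. This matches the first effectiveness research question.
- Test that comparison at two-sided 0.05, outside the MANOVA.
- List FSFI, IIEF, CES-D, BSI and SF-36 as secondary, so that the outcome section agrees with the abstract.

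The cost is wording in the protocol or SAP; every measure is still collected. The small downside is that an effect on a secondary scale alone can no longer be presented as confirming the trial.

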**Discussion:**

The proposed research project will be the first study to provide preliminary data about the effect and cost-effectiveness of brief sex counselling in youth in comparison with intensive sexological treatment and delayed treatment. It is anticipated that positive results in (cost-) effectiveness of the proposed intervention will contribute to the improvement of sexual health care for adolescents and young adults.

**Trial registration:**

The study has been registered at the Netherlands Trial Register, part of the Dutch Cochrane Centre (NTR1952)

## Background

Sexual health of adolescents has gained more attention over the last years [1,2]. Sexual health is described by the World Health Organisation (WHO) as:

"... a state of physical, emotional, mental and social well-being in relation to sexuality; it is not merely the absence of disease, dysfunction or infirmity. Sexual health requires a positive and respectful approach to sexuality and sexual relationships, as well as the possibility of having pleasurable and safe sexual experiences, free of coercion, discrimination and violence. For sexual health to be attained and maintained, the sexual rights of all persons must be respected, protected and fulfilled [3]".

The past decade has also seen a growing recognition of the existence of romantic relationships, experiences and sexual activities in adolescents [4]. With this attention some developments have taken place that could compromise the sexual health and romantic relationship capacities of adolescents.

The first development is the increasing proportion of young people that have sexual intercourse before the age of 16 [5]. Sexual intercourse before this age is associated with increased risks [6]. Men and women who had their first sexual encounter before the age of 16 show increased regret of this experience [5,7,8]. For both, boys and girls, the early onset of intercourse was associated with the experienced pressure by peers, and in girls this was also associated with the lack of control in the process of and during sexual intercourse [5]. Another study found increased rates of coercion to have sex in women who had their first sexual intercourse at a younger age. It is also found that the incidence of sexually transmitted diseases (STD's) was higher for the group who had their first sexual intercourse before the age of 16 [6,7]. Girls who began sexual activity before the age of 13 were twice as likely to become infected with an STD as girls who started sexual activity after the age of 21. Other associations of early sexual activity were a greater likelihood of becoming a single mother, more abortions, and lower levels of personal happiness [6].

Furthermore the younger a person was at his/her first sexual intercourse the higher the likelihood was of having multiple sex partners (at least five sex partners lifetime or four sex partners during the last six months). Having multiple sex partners is associated with (sexual) risk behaviours such as unsafe sex (not using contraceptives), smoking, drug- and alcohol use [8-11].

As mentioned before, unsafe sex is a common risk factor among adolescents and young adults. It has been found that only in the US, in 19 million new STD cases that occur every year, half of these are in individuals between 15 and 24 years of age [12]. Pregnancy is of course another consequence of unsafe sex. Darroch, Frost and Singh (2001) found that the US has the highest pregnancy and birth rate in women between 15 and 19 years compared to other developed countries. These higher rates arise primarily because of less, and probably less effective contraceptive use [13].

It is well known that mood disorders, and especially major depressive disorder, are among the most common mental disorders in adolescence [14-16]. Mental disorders, including depression, play a role in the development of sexual risk behaviour and sexual health problems [17,18]. Sex- and drugs-related behaviour predicts an increased likelihood of depression. Among girls, both experimental behaviour patterns (experimenting with sex, drugs and alcohol) and high-risk behaviour patterns (excessive drinking and/or drug use, and unprotected sexual contact) were found to increase the odds of subsequent depression. Among boys only high-risk behaviour patterns increased the odds of the development of subsequent depression [19].

Romantic attractions, activities (dating, kissing, more than kissing (like touching each other), etcetera) and relationships were also associated with a greater risk of depressive symptoms in adolescence [4,20]. Adolescents who had romantic relationships and who engaged in romantic activities, compared with adolescents who had not, reported increased depressive symptoms over time [21]. Several models have been proposed to explain this association. For example, the attention impairment model [22], suggests that romantic activities takes attention away from other important areas of functioning and so causing impairment, which increases the risk for depressive symptoms. Impairment of romantic functioning (interpersonal skills in the romantic domain) impaired by depressive symptoms can furthermore have far reaching consequences for the relational development of adolescents [4].

Another study in 7^th^-12^th ^grade students, age 13 to 18, found that depressive symptoms were associated with increased sexual risk. Among boys depressive symptoms were associated with non condom use at last sexual intercourse, among both boys and girls it was associated with a history of STD [17,23]. Thus, the relationship in adolescents and young adults between sexual behaviour and sexual risk behaviour on the one hand, and psychopathology, particularly depression, on the other hand, appears to be bidirectional.

In the Netherlands, adolescents are - in general - sexually healthy but there are some alarming developments. Bakker, et al. (2009) examined the sexual health of 6428 men and women between 15 and 70 years old (girls 15-18 years old N = 443; boys 15-18 years old N = 368). Of the 15 and 16 year olds, 33% of the girls and 25% of the boys had sexual intercourse. At the age of 17-18 these percentages have almost doubled. Girls with a lower education level have significantly more sexual experience than higher educated girls. Of the 15 to 18 year olds, 3.8% of the boys, and 2.9% of the girls have had more than 10 sexual partners up to that point of their lives. Furthermore, 32.6% of these boys and 28.5% of these girls experienced feelings of guilt about their sexual behaviour. Pregnancy and birth control were also examined in this study. Among boys, 1.1% of their female sexual partners had been pregnant and 0.4% had the baby. More of the partners of high-educated men under 26 years of age who experienced unwanted pregnancy had abortions than low educated men, but the partners of the latter more often gave childbirth. Among girls, 3.7% had been pregnant and 0.8% had the baby. Low educated girls under 26 years of age had more (unexpected) pregnancies, children, and abortions than high educated girls. Among boys, 58.9% uses no contraceptives, while this is the case for 40.9% of the girls. Sexual victimization is more common among girls than among boys (20.2% vs. 2.3%) [24]. Comparable results have been found in other studies in the Netherlands [1,25].

To improve this situation the Dutch national government has created a new service that facilitates assistance in the area of young peoples' sexual health. The core is a nationwide network of sexual health service provision centres (called 'Sense') for young people up to 25 years of age with questions concerning or problems with sexual health. The regulation builds on the experiences of the pilot version of Sense (pilot from 2005-2008), which was situated in three areas. One of them being the southern South-Holland (sSH) region. In the pilot version of Sense sSH, the Rotterdam-Rijnmond Public Health Service (PHS) identified an omission. Referral of adolescents with sexual health problems could not be performed adequately; the threshold for referral is too high (for example too expensive, too far away, etcetera). Research has shown that not everyone who needed help or advice for sexual health issues actually sought or had access to that help. The unfamiliarity with the available resources is one factor. Furthermore, the lack of trust in the available help, the costs, and reluctance of the help-seeking person are factors that play a role [24]. This implies that a large group of young people who need help for sexual issues have no access to the necessary care. For this reason the Rotterdam-Rijnmond PHS has, in addition to Sense, appointed a sex counsellor who helps to address the sexual problem in a maximum of three, free of charge and anonymous consultations of 45 minutes maximum. This service is called brief sex counselling. Its aim is to provide tailored and practical advice and/or reference to specialised health care, and to bridge the gap between Sense and this, more intensive, specialized help.

The earlier mentioned developments [24] regarding sexual health and the related mental health problems [17,18] form a major problem for youth in the Netherlands. Brief sex counselling might be a solution as it aims to treat the sexual problems of these adolescents in an early stage. Related mental disorders (like depression) would be less likely to develop or escalate. It is expected that brief sex counselling will prevent more serious and chronic problems in the future. However, there is no scientific evidence yet.

Goldmeier and colleagues calculated that, in 2004, the average costs of the treatment of sexual dysfunctions in the UK for women were €417 when delivered by a psychologist and €896 when delivered by a sex therapist [26]. Potentially, a certain proportion of patients with sexual problems do not require this type of intensive and costly treatment, but can adequately and satisfactorily be treated with less intensive and lower-cost alternatives. For instance, in the Netherlands it was estimated that 14% (respectively 56,000 of the extrapolated total of 400,547) of the patients treated in hospital outpatient clinics for sexology and 24% (respectively 80,500 of the extrapolated total of 335,594) of the patients treated in mental health care centres, could be adequately treated with a cheaper, low-threshold intervention [25,27]. It can be expected that brief sex counselling is a cheaper and more approachable option to treat sexual problems in adolescents than standard sexual health care provided in community mental health services or hospital outpatient clinics for sexology.

There are two main reasons to conduct this study that are related to current policy aims to improve the sexual health in youth. First, it can be assumed that brief sex counselling for high risk groups has a preventive impact on the recurrence of their sexual condition. This would reduce, moreover, the patient flow to more expensive health care in hospitals and mental health care institutions [25]. Second, a secondary prevention effect of sex counselling on mental health problems, in particular depression, is predicted [25,28].

The objectives of the current study are threefold. The first is the development of protocols for brief sex counselling in the field of sexual health to address problems in sexual functioning in youth. Furthermore a training plan will be developed to train nurses and public health workers to implement these protocols for brief sex counselling. The second objective is to investigate the effects of brief sex counselling on somatic, mental and sexual health. The third and last aim is to investigate the cost-effectiveness of brief sex counselling. We will examine whether brief sex counselling is preferable to more intensive formats of sexual health care and delayed treatment in terms of costs, impact and utilities from a social perspective.

